### Data collection

#### Circadian rhythm monitoring from saliva samples

Saliva samples will be collected by the participants at home using home-kits. As a good practice for structuring circadian studies several parameters will be considered, such as sampling frequency, number of repetitive cycles or sources of biological specimen [47, 48]. For saliva collection a home kit from TimeTeller^®^ (TimeTeller GmbH, Hamburg, Germany) will be used, and sample collection carried out following the instructions of the provider, according to the previously established sampling protocol and RNA extraction and quantification [34]. During sampling, participants are advised to carry out their normal daily routine and collect a total of 8 saliva samples (with 4-hours sampling interval e.g., Day1: 9 a.m.; 1 p.m.; 5 p.m.; 9 p.m.; Day 2: 9 am; 1 p.m.; 5 pm; 9 pm) during each sampling round (**Fig 1B**). Participants are advised not to drink or eat 1 hour prior to their sampling time. The samples should be directly shipped to the lab for analysis using an enclosed package. Should this not be possible, the samples can be stored at room temperature, for a few hours or at 4°C for short-term (up to a week) or at -20°C (refrigerator) for long term storage, till shipment is possible. Further analysis including RNA quantification will be carried out by TimeTeller^®^, and the results provided in the form of individual circadian profiles.

#### Hormonal assessment

Hormonal assessment includes quantification of melatonin, a hormone that peaks at night and promotes sleep, and cortisol, which depicts higher values in the morning contributing to increased alertness. For these measurements additional saliva samples will be collected, using home-kits from cerascreen^®^ (cerascreen GmbH, Schwerin, Germany). As indicated by the provider, for melatonin 1 ml saliva will be collected in the evening before the participant goes to bed. For cortisol analysis 7 samples with 1 ml of saliva each, distributed over the course of the day, from waking up till going to bed, will be collected. The results for hormone quantification are obtained from cerascreen^®^ in the form of a report for each participant. This information can then be used to draw a correlation between collected hormonal data and gene expression obtained from saliva samples. For each participant, sampling will be repeated at least once in Spring/Summer and once in Autumn/Winter, to determine the influence of seasonal effects. To avoid possible interference with sample collection, participants are asked not to eat or drink for 30 minutes before saliva collection. In addition, it is not recommended to brush teeth or use mouthwash before sampling to avoid these interfering with the sampling.

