The assessment of a dysregulated clock and its implication in disease requires the characterization of a healthy clock. The CR varies among individuals [16] and additional features such as sex, age or environmental influences (e.g., seasons) need to be considered. Females tend to exhibit an earlier circadian peak phase as compared to males, and previous reports showed a different therapeutic impact among females and males in colorectal cancer patients treated under chrono-modulated therapy regimes [17, 18]. Aging may also influence the CR resulting in dampening of the circadian amplitude, an advance of circadian phase, or result in gain or loss of rhythmic circadian expression [19–24]. Recent transcriptomics studies further revealed differential regulation of circadian gene expression between middle/older aged individuals, and younger adults [23, 25]. CR also fluctuate as a result of seasonal changes in light exposure as measured in sleep onset/offset times and duration [26, 27].

Monitoring the CR is possible via different methods, depending on the particular aim of the study, ranging from questionnaires to hormonal assessment via cortisol or dim-light melatonin onset [28–30]. These methods however, do not assess the molecular clock, or are time consuming and require medical assistance. Thus, a user-friendly and non-invasive method to assess the CR is advantageous. In this regard, the use of saliva-based methods, like TimeTeller^®^ [31] used in this study allows to assess gene expression profiles [31–33], and can be used to monitor the CR in humans [31–34]. The system-level regulation of the clock imposes optimal time frames for daily activities. Published data indicate an influence of circadian regulation on the physical performance for example, for professional athletes [35–37].

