#### Explorative objectives

Investigation of the possible association between CR and the expression of up to 800 target genes using a multiplexing system (using a nanostring nCounter SPRINT Profiler) will be performed on a subset of individuals to allow a comparison between different age groups within the cohort. The detection of the possible association between melatonin/cortisol level and the CR is an additional explorative objective.

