#### Explorative outcome measures

Additionally, clock and clock-related genes will be measured using a nanostring nCounter SPRINT Profiler using gene expression panels (Homo Sapiens Metabolic Pathways and a custom designed panel based on Extended Core Clock Network [55]) in a subset of participants to allow a better comparison of aging associated alterations of CR expression. By hormonal measurement at two different times of the year, the correlation between core-clock gene expression, cortisol and melatonin measurements will be investigated. The correlation between circadian gene expression and physiological parameters (daily activity measurements, heart rate, sleep) obtained by fitness trackers provided to the participants, will be explored.

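### A single pre-bed melatonin sample mixes level, rhythm timing and self-chosen sampling time, so the seasonal contrast and gene correlations may partly reflect bedtime and need a time-adjusted analysis

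*Protocol article*

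**What the plan says.** All references are to the protocol article.

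- **Sampling (Hormonal assessment).** "for melatonin 1 ml saliva will be collected in the evening before the participant goes to bed". No clock time, interval to habitual sleep or light condition is given. The same section contrasts with this for the other hormone: "For cortisol analysis 7 samples with 1 ml of saliva each, distributed over the course of the day".
- **Season (Hormonal assessment).** For each participant, "sampling will be repeated at least once in Spring/Summer and once in Autumn/Winter, to determine the influence of seasonal effects". A participant may therefore contribute as few as two melatonin values.
- **Use.** Explorative objectives: "The detection of the possible association between melatonin/cortisol level and the CR is an additional explorative objective". Explorative outcome measures: "the correlation between core-clock gene expression, cortisol and melatonin measurements will be investigated". Analysis for secondary endpoints plans correlations that include the hormonal data and mentions no term for sampling time.
- **Background.** The Introduction lists "hormonal assessment via cortisol or dim-light melatonin onset" among existing ways to monitor the rhythm. It also says that seasonal changes in light exposure show up in the timing and duration of sleep.
- **Times recorded.** Data management asks participants to note exact saliva sampling times and their wake and sleep times on sample collection days. Digital questionnaires includes the µMCTQ.

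**The concern.** Melatonin rises through the evening, so a pre-bed concentration depends on how far the rise has progressed when the sample is taken, as well as on how much melatonin the person makes. Two people with the same rhythm and different bedtimes return different values, and so does one person whose bedtime moves between seasons.

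Bedtime is not a neutral source of noise here. The Introduction links sleep timing to season, and season is the contrast for which the hormone sampling is repeated. Bedtime may also be related to the gene-expression phase with which melatonin will be correlated. An unadjusted result could therefore be taken for a seasonal or circadian change in melatonin when part of it is a change in when the tube was filled.

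**Working it through.** The plan gives no figure for melatonin: no spread of bedtime, phase or amplitude, and no expected effect. Its sample size (52, or 59 with 12% dropout) is for rhythmicity of *BMAL1* and does not bear on this point. Everything numerical below rests on stated assumptions.

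**1. What one sample can identify.** Primary outcome measure describes a rhythm by phase, amplitude and mesor, which is three parameters. In a cosinor model each sample adds one row (1, cos ωt, sin ωt) to the design matrix. One sample gives rank 1 of 3; seven samples spread over the day give rank 3. Melatonin phase and amplitude are not estimable from the planned sample.

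**2. Timing and level trade off.** Assume a cosine with its peak at 03:00, value = A × [1 + cos(2πh/24)]/2, where h is hours before the peak.
- At 23:00, h = 4, value 0.750 A.
- Bedtime 1 h later (h = 3): 0.854 A.
- Bedtime unchanged, rhythm 1 h earlier (h = 3): 0.854 A, the same number.
- A peak at 01:00 (h = 2, factor 0.933) gives the same 23:00 value if A is 0.750/0.933 = 0.80 of the reference. A peak at 05:00 (h = 6, factor 0.500) does so if A is 0.750/0.500 = 1.50.

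**3. Seasonal contrast with an unchanged rhythm.** Let bedtime move later by d hours from 23:00.
- Cosine ratio: [1 + cos(2π(4 − d)/24)] / [1 + cos(2π·4/24)].
- Steep rise: the ratios below are those of a logistic rise of 1.5 per hour sampled 0.5 h after its midpoint, (1 + e^(−0.75)) / (1 + e^(−0.75 − 1.5d)).

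| d (h) | Cosine | Steep rise |
|---|---|---|
| 0.25 | 1.037 | 1.112 |
| 0.5 | 1.073 | 1.204 |
| 1.0 | 1.138 | 1.332 |

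That is about 4% to 14%, or 11% to 33%, with no change in the rhythm.

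**4. How much of the between-person spread could be bedtime?** Assumed ranges: bedtime SD 0.5, 1.0 or 1.5 h; phase SD 0.5 or 1.0 h; bedtime-phase correlation 0, 0.5 or 0.8; amplitude CV 0.3 or 0.6; cosine or steep rise; no assay error. This makes 3 × 2 × 3 × 2 × 2 = 72 scenarios.
- Bedtime alone explains 0% to 64% of the variance of log melatonin, and more than 50% in 5 of 72, all with the steep rise.
- The share that bedtime adds once phase and amplitude are known reaches 67%, and exceeds 50% in 9 of 72, again all with the steep rise.
- In many of the other scenarios amplitude or phase dominates.

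**5. What adjustment does to the phase signal.** It can move either way. With the steep rise, bedtime SD 1.0 h, phase SD 0.5 h, correlation 0.5 and CV 0.3, phase explains 0% alone and 16% once bedtime and amplitude are held fixed. With bedtime SD 1.5 h and correlation 0.8 (phase SD and CV the same), it falls from 25% to 5%.

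**The case against.** The strongest points on the other side are these.

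- **The plan does not promise a melatonin rhythm.** Explorative objectives speaks of a level. Dim-light melatonin onset appears only as background, in a paragraph that goes on to list drawbacks of such methods. This stands: a reader might infer that the plan offers onset or phase from this sample, and no section says so. It does not dispose of the point, because the level itself depends on sampling time and a seasonal purpose is stated.
- **The seasonal repeat is within person.** Stable differences in chronotype or amplitude cancel in a paired contrast. This stands, and leaves only a seasonal change in the interval between the melatonin rise and bedtime. That is the quantity in step 3.
- **An article condenses the plan.** Covariates for an explorative correlation may sit in an analysis plan that is not shown. This stands for the missing covariate taken alone. The sampling scheme and its seasonal purpose, however, are fixed in the text, and if the adjustment is already written elsewhere the fix costs nothing.
- **Bedtime tracks internal phase.** Adjusting for it may remove part of the association being explored. This stands (step 5) and argues for showing both analyses rather than replacing one with the other.
- **Low consequence.** The aim is explorative. This limits how much the point matters, not whether it is right.

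**Conclusion.** The point holds in a limited form. One pre-bed value cannot give melatonin phase or amplitude. An unadjusted seasonal contrast or gene correlation may partly reflect bedtime. The first statement follows from the design alone. The second rests on the Introduction's own link between season and sleep timing, and its size is unknown: 4% to 14% or 11% to 33% for a shift of 0.25 to 1 h, under assumed curves and an unchanged rhythm.

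Three stronger readings are tempting and are not supported:

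- *That the melatonin results would mostly measure bedtime.* The documents give no spreads, and under the assumed ranges bedtime's share runs from negligible to dominant, passing one half in few scenarios.
- *That an hour of bedtime changes the value by 20% to 90%.* A half-sine rise over 12 h, sin(πh/12), gives ratios of 1.93, 1.41 and 1.22 for successive hours from 1 to 4 h after onset. But it starts from zero with no baseline, holds the rhythm fixed and stops at 4 h; the next two ratios are 1.12 and 1.04.
- *That age differences in melatonin are at risk.* The planned age comparisons concern gene expression. Season is the only stated melatonin contrast.

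The primary endpoint, the success criterion and the sample size are untouched.

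**What to change.** 1. **Analysis for secondary endpoints:** analyse log pre-bed melatonin with the recorded clock time of the sample as a covariate, within person for the seasonal contrast, and report it beside the unadjusted result. State whether clock time is local or standard time: Study design splits the seasons at the daylight-saving change, so the adjusted season effect depends on that choice.
2. **Sensitivity analysis only:** add the interval to habitual sleep onset from the µMCTQ. It is itself related to phase, so it should not be forced into the main model.
3. **Hormonal assessment and Explorative outcome measures:** call the variable a pre-bed melatonin concentration, and say that neither the correlation nor the seasonal contrast is evidence of a change in melatonin phase or amplitude.
4. **Data management:** confirm that the recorded sampling and sleep times cover the days on which the hormone kit is used. The text does not say so explicitly.

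The cost is one covariate, possible attenuation where bedtime follows internal phase, and a narrower exploratory claim. No further samples are needed if item 4 is confirmed. Adjustment reduces the bedtime component but does not make phase and amplitude separable, which is why item 3 is needed as well as item 1.

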#### Remote participant monitoring (wearable devices)

In the beginning of the study, participants will be provided a Xiaomi Smart Band 6 (MiBand 6, Xiaomi, Inc). This wrist-worn device monitors parameters such as heart rate, sleep and activity. Data from MiBand devices will be collected in real-time and synchronised with the application installed on the participant’s smartphones via Bluetooth. For this study, a cost-efficient and user-friendly smart wearable alternative was chosen, which has been previously reported to yield reasonable accuracy and precision of the outputted parameters and therefore appropriate for usage in the context of scientific research [49–51]. The participants will be advised to wear the watch at least the day before starting the saliva sampling; heart rate and sleep-wake rhythm will be recorded throughout the day. ZeppLife app will be used to export data from trackers by the participants, which will be provided to the study team using a secured folder stored at the University servers.

#### Digital questionnaires

Questionnaires and medical history will be collected by the participants in eCRF (electronic case report form) format distributed via Research Electronic Data Capture (REDCap) to preserve protected flow of information. This data will be collected at least twice within 4 total repetitive saliva sampling rounds (one in Spring/Summer and one Autumn/Winter batch maximum per participant). The general medical history is asked regarding the following: presence of known chronic or acute diseases; medications; smoking habits; presence of shift work in the past 3 months, and several questionnaires which include the μMCTQ (An Ultra-Short Version of the Munich ChronoType Questionnaire) [52] to assess the chronotype based on the core module questions of the original Munich ChronoType Questionnaire; the PSQI (The Pittsburgh Sleep Quality Index) a questionnaire to assess sleep quality [53] and the International Physical Activity Questionnaire to evaluate the physical activity patterns of participants [54], which will be used to categorize participants according to the collected questionnaire results, and may subsequently be correlated to gene expression changes. Participants will access the survey using the link provided to them, and generated using the tool REDCap, as described above, from any internet connected device (mobile or computer). Each participant can only fill their own data, during their sampling days, in pseudonymized form (using the participant codes provided by the study team), and cannot access data from another participant.

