In this study, we aim to characterize and monitor the circadian clock with respect to sex in healthy individuals for different age groups, including teenagers (≤18 years old); younger adults (18–40 years old) and older (>40–60 years old individuals across the year via measurement of core-clock and CCGs in saliva samples. We will analyze participants with respect to additional factors based on characteristics like the chronotype, mid-sleep time, and activity scores, or frequency of sick-related absence at work, to explore a potential correlation among these different factors and gene expression changes of circadian genes. In addition, to characterize a healthy CR, we aim to combine such data to obtain a comprehensive profile of optimal performance for participants, which can potentially be generalized to other individuals with similar CR profiles. We will complement our analysis with other physiological parameters including hormonal data from melatonin, which has been reported to depict high values during the night thereby promoting sleep, and cortisol with high levels in the morning, promoting alertness. Given the increase usage of wearables and its potential for assessment of daily oscillations [38], we will also collect smart tracker data and monitor parameters such as activity, for each participant and search for significant correlations with the gene expression data.

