#### Secondary objectives

Using the collected activity tracker data in parallel to the saliva sampling, a correlation analysis will be carried out between CR and the activity data. An additional subgroup analysis based on the questionnaire and medical history results and gene expression changes will be carried out. For the analysis, we plan to also include data from our previous study (Basti *et al*. 2021 [34]) in which participants carried out physical activity tests at different times of the day. This data set will be used to support the development of predictors for establishment of the optimal time intervals for physical exercise.

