#### Sample size estimation

Sample size calculation was performed based on *BMAL1* gene expression data from our previous work [34] assuming that all measurements follow a sinusoidal wave function $y_{i}=A\;sin\;(\omega (t_{i}+\phi ))+M+\varepsilon_{i}$, 1 ≤ i ≤ n whereby n is the total number of samples, $\omega =\frac{2\pi }{Period}$ the frequency of the sinusoidal wave, φ the phase shift, M the rhythm-adjusted mean (MESOR), and t_i_ the observed Zeitgeber time. ε_i_ is the error term for sample i. We assume ε_i_ are identically and independently distributed from $\varepsilon_{i}∼N(0,\sigma^{2})$, where σ is the noise level. The null hypothesis that there is no circadian rhythmicity (H_0_ = 0) is tested against the alternative hypothesis that a circadian rhythmicity pattern exists (H_A_≠0). Rhythmicity will be tested using the F-test which compares the fitted model against a restricted model. For details see please Cornelissen [39]. The study is considered successful if rhythmicity is detected in the measured core-clock and clock-controlled genes obtained from saliva samples. To account for multiple comparisons (comparisons between gender and age subgroups and various seasons, in total up to 10 comparisons) the type I error is set to 0.005 according to the Bonferroni correction to hold the global significance level of α = 0.05. Underlying the data of our previous study [34], an amplitude (A) of 1.11 is estimated for *BMAL1* gene expression and the standard deviation of residuals (s) is 1.36, which gives an estimate of the intrinsic effect height of r = A/s = 0.82.

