In order to detect an intrinsic effect of r = 0.82 as significant at α = 0.005 and achieve a power of 0.8, a sample size of 52 is necessary (**Fig 2**). The sample size was estimated by R package CircaPower [40]. A dropout rate of 10–15% [41–44] is generally considered for calculating the sample size in clinical studies although there is no universal filter. As a compromise for potential higher dropout due to the longitudinal design of our study, we considered a dropout of 12% in our sample size estimation, and calculated a population of 59 participants to be sufficient to allow for the planned comparisons in the subset of a) females vs males or b) age groups or c) seasons. Participants will be distributed evenly for comparisons (e.g., for sample size) or appropriate statistical measures will be taken, by using statistical tests considering unequal sample size. Participants for whom there are no saliva samples collected are considered as dropout.

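### The questionnaire analysis is described firmly as grouping participants and only loosely as correlating scores; the article should say that the numeric scores are the explanatory variables, because groups in their place would lose information

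*Protocol article*

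**What the plan says.** Three places in the protocol article bear on this point.

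- **Digital questionnaires** (Data collection): the chronotype, sleep-quality and physical-activity questionnaires are collected, "which will be used to categorize participants according to the collected questionnaire results, and may subsequently be correlated to gene expression changes". Grouping is stated as certain; the link to gene expression is stated as possible and comes afterwards.
- **Secondary objectives**: "An additional subgroup analysis based on the questionnaire and medical history results and gene expression changes will be carried out". This is a commitment, and it is to a comparison of subgroups.
- **Introduction**, last paragraph: participants will be analysed by "additional factors based on characteristics like the chronotype, mid-sleep time, and activity scores", with the purpose "to explore a potential correlation among these different factors and gene expression changes of circadian genes". This can be read as correlating the values themselves.

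The section Analysis for secondary endpoints lists correlations of molecular data with exercise, hormonal and tracker measurements and does not name the questionnaires. It does plan circadian curves for each individual and sampling round, for exploratory use. No cut-points, number of categories, effect size, alpha or power are stated for the questionnaire analysis.

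**The concern.** Mid-sleep time and activity scores are numeric as the Introduction describes them. Once they are cut into groups, differences between participants within a group no longer count, and the result depends on where the cut falls. With a target of 59 participants there is little information to spare. Uneven cuts cost more than even ones. Uneven activity groups are plausible because recruitment runs through a sports club and otherwise asks about physical activity, but the article gives no distribution, so this is conjecture. At stake is the chance of seeing a real relation between questionnaire scores and circadian gene expression in data the study will already hold.

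**Working it through.** **The plan's own figure.** The only power statement concerns *BMAL1* rhythmicity: "the type I error is set to 0.005 according to the Bonferroni correction", an effect "which gives an estimate of the intrinsic effect height of r = A/s = 0.82", and to "achieve a power of 0.8, a sample size of 52 is necessary". For the cosinor F-test with 2 and n − 3 degrees of freedom and noncentrality n·r²/2 (evenly spaced sampling), n = 52 gives 52 × 0.82² / 2 = 17.5 and power 0.800. The stated N reproduces. The r in that calculation is amplitude over residual SD, not a correlation with a questionnaire score, so it says nothing about the power of the questionnaire analysis.

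**Inputs for the check.**
- From the article: n = 52, and 59 after the 12% dropout allowance.
- Assumed, not in the article: a normally distributed score, a linear relation, one value per participant, two-sided alpha 0.05, and a true correlation ρ that gives 80% power when the score is kept numeric.

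**Formulas.** Power ≈ Φ(√(n − 3) · atanh(ρ) − 1.96). Cutting a normal score at c into proportions p and 1 − p multiplies ρ by k = φ(c)/√(p(1 − p)). For a median split, k = 0.399/0.5 = 0.798, and k² = 2/π = 0.64. That is the share of information kept, equivalent to losing about 0.36 × 59 ≈ 21 participants.

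**Example, n = 59.** With ρ = 0.358, √56 × atanh(0.358) − 1.96 = 0.84 and Φ = 0.80. After a median split, ρ becomes 0.798 × 0.358 = 0.286; √56 × atanh(0.286) − 1.96 = 0.24 and Φ = 0.59.

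| Score used as | k | Power, n = 59 (ρ = 0.358) | Power, n = 52 (ρ = 0.380) |
|---|---|---|---|
| Number | 1 | 80% | 80% |
| Three equal groups, ordered trend | 0.891 | 69.5% | 69.4% |
| Median split | 0.798 | 59% | 59% |
| 70/30 split | 0.759 | 55% | 55% |
| 80/20 split | 0.700 | 48% | 48% |

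A simulation with 20,000 replicates agrees to within about 2 points: at n = 59 it gives 81% numeric, 71% ordered trend, 61% median split and 49% for 80/20. Three equal groups compared by an unordered F-test give 60%.

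**How far the result depends on the assumed correlation** (median split, n = 59, alpha 0.05):

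| ρ | Numeric | Split | Loss (points) |
|---|---|---|---|
| 0.2 | 33% | 23% | 10 |
| 0.3 | 64% | 45% | 19 |
| 0.4 | 89% | 70% | 19 |
| 0.5 | 98% | 89% | 10 |
| 0.6 | 99.9% | 97% | 2.5 |

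**How far it depends on alpha.** The article's 0.005 is budgeted for the sex, age and season comparisons, so it serves only as a sensitivity case here. With 80% reference power at n = 59 (ρ = 0.452), the losses are 15 points for an ordered trend over three equal groups, 29 for a median split and 44 for 80/20.

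**The case against.** The strongest reply is that the article never says categories replace scores. In the Digital questionnaires sentence it is the questionnaires that may be correlated, so grouping and correlating can be read as two separate uses, and the Introduction supports that reading. Coding of variables and cut-points for an optional, additional analysis is also commonly left to a fuller document that is not shown. Both points stand as far as they go: missing cut-points are no fault here, and the article cannot be said to have fixed the worse method. What remains is that the wording it does commit to is the grouped one, and that it does not match the Introduction.

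A reader might go further and infer that the study will lose some 20 to 30 points of power. The documents do not support that as a property of this study. It follows only for a two-group cut, or an unordered three-group test, at 80% reference power. Three ordered categories lose about 10 points, and other correlations give a median-split loss of 2 to 20 points over n = 52 to 59.

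Further limits also stand. One value per participant simplifies a design with questionnaires at least twice and up to four sampling rounds. The article does not give the scale of the sleep-quality index, so treating it as numeric is an assumption. Regression on scores needs rhythm parameters for each individual, each from 8 samples per round, whereas a group comparison can pool samples; the calculation gives both approaches the same outcome noise and does not model this. Phase is circular, so ordinary linear regression does not apply to it directly.

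**Conclusion.** The point holds as a minor improvement. The article states grouping and subgroup comparison as definite and correlation as optional, and its Introduction points towards correlating the values. If categories stand in for the numeric scores, power would fall from 80% to about 59% (median split), 55% (70/30), 48% (80/20) or 69% (three ordered categories as a trend), on the assumptions listed in the check. None of those assumptions comes from the article, so the figures illustrate the cost of a choice and are not an estimate of what this study will lose. The analysis is exploratory and has no power target. The primary endpoint, N = 52 and the sex, age and season comparisons are unaffected.

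**What to change.** State in Secondary objectives and Digital questionnaires that the numeric scores (mid-sleep time, sleep-quality score, activity score) are the explanatory variables for the per-individual rhythm parameters already planned under Analysis for secondary endpoints, and that categories serve for description. Add that phase is handled as a circular quantity, that repeated rounds from one participant are treated as correlated, and that a curvature term checks the linear form.

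The cost is a few sentences and somewhat more modelling, with no new data, samples or participants. The small downside is that results are expressed per unit of score rather than per named group, and rest on individually estimated rhythm parameters.
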